### Strategies to improve adherence to interventions {11c}

We will document and reinforce adherence during each study visit. Participants will complete a dosing journal (self-documentation) and return unused products; research staff will review the journal and number of remaining pills or sachets containing fiber or placebo to document adherence. Additionally, participants will be contacted regularly by email and text messages to reinforce adherence.

### Relevant concomitant care permitted or prohibited during the trial {11d}

Hypoglycemic drugs, insulin, and medications known to affect body weight will not be allowed during the trial. If a participant must use any of these medications, he/she will be withdrawn from the study. The principal investigator will determine acceptability of any other concomitant medication. Adolescents in this study will continue to receive conventional lifestyle management advice as per routine clinical practice at their clinics.

### Provisions for post-trial care {30}

There is no specified ancillary or post-trial care for participants in this trial. However, it is expected that the results of this study will guide clinical care of children at high risk of T2DM after completion of the trial. If a participant becomes ill or injured as a result of being in this study, he/she will receive necessary medical treatment, at no additional cost to the participant.

### Outcomes {12}

The primary outcome of this study is a change in IR, as estimated by HOMA-IR, between baseline, 6, and 12 months. The secondary outcomes of this study include changes between baseline, 6, and 12 months in (1) the Matsuda, insulinogenic, and oral disposition indices as determined by OGTT; (2) weight, BMI percentile and *z*-score, and body composition (fat mass, fat-free mass, and ratio of fat mass to fat-free mass); (3) QoL and perceived hunger and satiety; (4) fasting metabolic (glucose, adiponectin, lipids, and OGTT) and satiety markers (acylated ghrelin, PYY, GLP-1, and leptin); (5) measures of systemic inflammation (C-reactive protein, interleukin 6, and TNF-α) and gut barrier integrity (lipopolysaccharide-binding protein [LPB] and fecal calprotectin); and (6) gut microbiome composition and functions (fecal microbiome composition, fecal SCFAs and bile acids, and targeted plasma metabolomics [amino acids, branched chain ketoacids, acylcarnitines, ceramides, trimethylamine *N*-oxide, choline, and betaine]).

### Participant timeline {13}

#### Sample size {14}

Our primary outcome is IR as estimated by HOMA-IR. Based on a recent study where the effect size of MET on HOMA-IR among pubertal participants was 0.75 [49], we estimated a sample size of 29 per arm, which will give us 90% power to find any significant post-intervention difference between arms at 5% significance level. Additionally, a percentage of change and 95% confidence interval for HOMA-IR after PGX from Pal et al. [50] resulted in an effect size of 0.86, rendering a sample size of 26 per arm. We expect a greater response in the combination therapy; for this reason and considering 26 per arm as feasible, and 15% attrition rate during follow-up, we estimated a total of 90 participants over the 3 arms.

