### Trial design {8}

A single-center, parallel three-armed, double-blinded, 12-month randomized controlled trial with a 1:1:1 allocation ratio. Ninety adolescents (*n* = 30 per arm) with obesity, IR, and family history of T2DM will be enrolled in the trial matched for sex and age (Figs. 1 and 2).

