### Statistical methods

#### Statistical methods for primary and secondary outcomes {20a}

Descriptive statistics will summarize all study variables. Prior to analysis, numerical variables with skewed distribution will be transformed (e.g., log_2_ or cubed root) or a comparable nonparametric test will be used. Between-group comparison of primary and secondary outcomes will be performed at baseline and two consecutive time points independently using unpaired *t*-tests (comparing two groups) or analysis of variance (three groups) and chi-square tests for numerical and categorical data, respectively. Impact of the three interventions on IR (HOMA-IR, primary endpoint) over time will be compared using linear mixed models, after adjusting for relevant confounders, including pubertal stage if any statistically significant difference is observed between treatment groups at baseline. OTU relative abundance will be compared between treatment groups. Statistical analyses for gut microbiota community composition will include principal coordinates analysis and canonical correlation. Linear discriminant analysis Effect Size [78] and multivariate association with linear models will be used to identify specific OTUs that differentiate the treatment groups. Mediation modeling will be employed to provide further insights on possible casual pathways to explore whether the gut microbiota may play a causal or mediation role in the physiological effects detected [79]. Treatment responders versus non-responders will also be evaluated. We will characterize the ecological differences prior to the intervention, and then the individualized response to the intervention in order to assess the role of the microbiome in the host’s metabolic response to the intervention. For this analysis, we will apply a machine learning approach called partition around medoids clustering [80]. Separate models will be estimated for secondary endpoints, which are exploratory, but nevertheless important. Intervention types and times will be included as fixed effects in linear mixed models. Pearson or Spearman correlation coefficients will be computed between changes in gut microbiome composition/function and insulin resistance, hormones, metabolites, and inflammatory markers.

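### The stated 90% power does not follow from the protocol's own inputs: 29 per arm gives about 80% for an effect size of 0.75, and 90 randomised less 15% attrition gives about 75%

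*Protocol article*

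**What the plan says.** Protocol article, Sample size {14}, gives two derivations and then a total.

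- First: "the effect size of MET on HOMA-IR among pubertal participants was 0.75", from which "we estimated a sample size of 29 per arm, which will give us 90% power to find any significant post-intervention difference between arms", at the 5% level.
- Second: a cited PGX study "resulted in an effect size of 0.86, rendering a sample size of 26 per arm". No power is attached to this figure.
- Total: a greater response is expected with the combination, and, "considering 26 per arm as feasible, and 15% attrition rate during follow-up, we estimated a total of 90 participants over the 3 arms".

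Trial design {8} fixes equal allocation with 30 per arm. The section names neither the test nor its sidedness. Statistical methods {20a} plans unpaired t-tests ("comparing two groups) or analysis of variance (three groups") at each time point and linear mixed models for HOMA-IR over time. None of these is described as one-sided.

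**The concern.** The section prints effect size, sample size, significance level, power and attrition, so the calculation can be checked, and its parts do not agree. The number per arm tied to 90% power is the one that a standard calculation returns for 80%. The total is then built on a different, smaller number per arm, so even the 29 is not available after the attrition that the plan itself expects.

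A reader of the results would take the trial as having a 10% risk of missing the planned effect. If the risk is nearer 25%, a null result deserves much less weight than the protocol suggests. The Discussion anticipates use of the results in practice guidelines, so the figure matters.

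**Working it through.** **Inputs, all from Sample size {14} except the allocation.** Effect sizes d = 0.75 and 0.86; 29 and 26 per arm; 5% level; stated power 90%; attrition 15%; total 90; allocation 1:1:1 (Trial design {8}).

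**Assumptions.** The effect size is a standardised mean difference. The test is a two-sided two-sample t-test without baseline adjustment. Two-sided is the natural reading because the stated aim is non-directional and no one-sided test is planned.

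**Method.** Power from the noncentral t distribution with noncentrality d × √(n/2) and 2n − 2 degrees of freedom.

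**1. Attempt to reproduce 90% at 29 per arm, d = 0.75.** Noncentrality = 0.75 × √14.5 = 2.86, with 56 degrees of freedom. Power = 80.1% (81.5% by the normal approximation). Solving for n:

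- 80% power needs 28.9, so 29 per arm, which is the protocol's number.
- 90% power needs 38.3, so 39 per arm.

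**2. Other readings at 29 per arm, d = 0.75.**

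| Reading | Power | n per arm for 90% |
|---|---|---|
| Two-sided t-test | 80.1% | 39 |
| One-sided 5% t-test | 88.0% | 32 |
| Three-group ANOVA, third mean midway (f = 0.306) | 71.0% | 47 |
| Three-group ANOVA, two means equal (f = 0.354) | 83.5% | 35 |
| Three-group ANOVA, f = d/2 = 0.375 | 87.8% | 32 |

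The last row uses the two-group conversion. It slightly exceeds the largest f that three equal arms spanning 0.75 can have (0.354), so it is generous. No row reaches 90%.

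**3. The second figure, 26 per arm for d = 0.86.** Two-sided power is 86.0%. For 80% power n = 22.2, so 23; for 90% power n = 29.4, so 30. The stated 26 is neither.

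**4. Do 29 and 26 come from one calculation?** At fixed significance level and power, n is close to proportional to 1/d².

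- If 0.75 needs 29, then 0.86 needs about 29 × (0.75/0.86)² = 22.1.
- If 0.86 needs 26, then 0.75 needs about 26 × (0.86/0.75)² = 34.2.

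So the two figures were not obtained with the same level and power. This check hardly depends on the choice of test or sidedness.

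**5. Attrition.** 90 × 0.85 / 3 = 25.5 completers per arm.

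- To keep 26: 26/0.85 = 30.6, so 31 per arm, 93 in total.
- To keep 29: 29/0.85 = 34.1, so 35 per arm, 105 in total.

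Power at 25.5 per arm:

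| Effect size | Two-sided | One-sided |
|---|---|---|
| 0.75 | 74.7% | 84.0% |
| 0.86 | 85.3% | 91.7% |

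The smallest effect detectable with two-sided 80% power at 25.5 per arm is 0.80 per pairwise contrast; with 90% power it is 0.93.

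**6. Could baseline adjustment supply the missing power?** Adjustment multiplies the variance by 1 − r², where r is the correlation between baseline and follow-up. The r needed for 90% power is about √(1 − n/38), where 38 is the normal-approximation n for 90%. This is 0.49 at 29 per arm and 0.57 at 25.5. As a check with the t-test, r = 0.5 turns 0.75 into 0.75/√0.75 = 0.866, which has 90.0% power at 29 per arm. The protocol article states no such correlation.

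**The case against.** **Test and sidedness are not stated.** This is true, and the one-sided and most generous ANOVA readings come within about two points of 90% at 29 per arm. But neither returns 29 for 90% power, whereas the two-sided 80% calculation returns exactly 29. For the effect of 0.75, the one-sided reading drops to 84% after attrition.

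**The main analysis is a linear mixed model on repeated measures, so an unadjusted t-test understates power.** This stands as a limit on the conclusion. With a correlation of about 0.5, 29 per arm would reach 90%. It does not rescue the text, which neither gives a correlation nor says that one was used.

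**25.5 per arm is a completers' figure.** This also stands. Data up to withdrawal are kept, and intention-to-treat analysis is planned with multiple imputation or a sensitivity analysis. So 25.5 is a conservative planning number, not necessarily the number analysed.

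**Thirty rather than 31 per arm is trivial.** Agreed. Multiplying 26 × 3 = 78 by 1.15 gives 89.7, which probably explains the 90. The shortfall is half a participant per arm, and power at 0.86 moves only from 86.0% to 85.3%. The section also openly says why it settles on 26. What matters is that the 90% claim is tied to 29, which the total does not deliver.

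**Stronger inferences that the document does not support.** A reader might subtract 0.75 from 0.86 and conclude that metformin versus fiber has almost no power. The two figures come from different cited studies. The second is derived from a percentage change after PGX, which makes up 5 g of the 35 g mixture, so their difference does not estimate that contrast. Nor can one power be quoted for the combination beating both monotherapies, because the protocol gives no effect size for either comparison. And nothing here justifies demoting metformin versus fiber, which is part of the primary objective in Objectives {7}.

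**Conclusion.** The point holds as an arithmetic error in the sample size statement. With a standardised effect of 0.75 and a two-sided 5% two-sample t-test without baseline adjustment, 29 per arm gives 80% power, about ten points below the stated 90%. The planned 90 participants less 15% attrition give about 75% for 0.75 and 85% for 0.86 in a completers' analysis. The 29 and the 26 do not come from one consistent calculation, and the total was built on the 26.

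The exact shortfall depends on the test, the sidedness and any baseline adjustment, none of which the section states. The finding does not show that 90 participants are too few for the trial's purpose. It shows that the stated power is unsupported and that a 90% claim covering any difference between arms should not stand.

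**What to change.** Keep the total of 90 and rewrite Sample size {14} to say:

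- which test and sidedness were used, and that the effect sizes are standardised differences, if that is so;
- that 29 per arm gives 80% power for 0.75 with a two-sided 5% two-sample t-test;
- that 90 randomised with 15% attrition leaves about 25 completers per arm (25.5 on average), giving about 75% power for 0.75 and 85% for 0.86, with a smallest effect detectable at 80% power of about 0.80 per pairwise contrast.

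Remove the claim of 90% power for any difference between arms. If the investigators rely on a baseline-adjusted or mixed model for more power, they should state the assumed correlation and its source; about 0.5 is needed for 90% at 29 per arm, and more at 25.5.

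The cost is a wording change. The design, the number of participants and the primary objective stay as they are; the stated power becomes less favourable. The article reports that recruitment had not started, so at that date the change could precede enrolment.

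### The stated 90% power is wrong: 29 per arm at an effect size of 0.75 gives 80% (two-sided 5%, unadjusted); 90% needs 39 per arm

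*Protocol article*

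**What the plan says.** Everything on power stands in one paragraph of the protocol article, Sample size {14}.

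- The first input is a published metformin result: "the effect size of MET on HOMA-IR among pubertal participants was 0.75". From it the article concludes: "we estimated a sample size of 29 per arm, which will give us 90% power to find any significant post-intervention difference between arms", at a 5% significance level.
- The second input is a published PGX fiber result, which "resulted in an effect size of 0.86, rendering a sample size of 26 per arm". No power is printed beside this figure; the reader is left to carry over the 90%.
- The total follows from the second figure: "considering 26 per arm as feasible, and 15% attrition rate during follow-up, we estimated a total of 90 participants over the 3 arms". A greater response to the combination is given as a further reason.

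Trial design {8} confirms 30 per arm, allocated 1:1:1. The paragraph states no sidedness, no correlation between baseline and follow-up, and no adjustment for several comparisons. It does not define the effect-size unit.

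**The concern.** Effect size, number per arm, power and significance level are printed together, so they can be checked against each other, and they do not agree. Because the four figures are fixed in the text, this is not a detail that a separate analysis plan could supply.

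This is the only power statement for the primary outcome. Both comparators are active, and the comparison of interest is the combination against each monotherapy (Explanation for the choice of comparators {6b}). A non-significant result would be read against the stated power, that is, as carrying a 10% chance of having missed the assumed effect.

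**Working it through.** **Inputs, all from Sample size {14} unless noted.** Effect sizes d = 0.75 and d = 0.86; 29 and 26 per arm; 5% level; 90% power; 15% attrition; 90 in total, 30 per arm (Trial design {8}).

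**Assumptions.** The effect size is a between-arm difference divided by the SD. The test is two-sided, because the stated target is "to find any significant post-intervention difference between arms at 5% significance level" with no direction. Tests for two groups (unpaired t) and three groups (ANOVA) are those named in Statistical methods {20a}.

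**1. The plan's figure, d = 0.75.** By the normal approximation, n per arm = 2(z₀.₉₇₅ + z_power)²/d².

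- 80% power: 2(1.960 + 0.842)²/0.75² = 27.9; the t-test solution is 28.90, so 29 per arm.
- 90% power: 2(1.960 + 1.282)²/0.75² = 37.4; the t-test solution is 38.35, so 39 per arm.
- Power at 29 per arm: 80.1% (t-test), 81.5% (normal).

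The stated 29 is therefore the 80% answer.

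**2. Other unadjusted between-arm readings at d = 0.75, 29 per arm.**

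| Reading | Power |
|---|---|
| One-sided 5% t-test | 88.0% (90% needs 31.15, so 32) |
| Three-arm ANOVA, one arm differing, f = 0.75·√2/3 = 0.354 | 83.5% |
| Three-arm ANOVA, middle arm midway, f = 0.75/√6 = 0.306 | 71.0% |

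With three equal arms and a largest difference of 0.75 SD, f cannot exceed 0.354. A paired t-test with 29 gives 97.4%, but that is a within-arm test and the text speaks of a difference between arms.

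**3. Do the two sizes come from one calculation?** At a fixed level and power, n is proportional to 1/d². The ratio should be (0.86/0.75)² = 1.31. The stated ratio is 29/26 = 1.12. For d = 0.86 the t-test needs 22.23 (so 23) for 80% and 29.41 (so 30) for 90%; 26 per arm gives 86.0%.

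**4. Power with 90 randomised (two-sided t-test, unadjusted).** Completers per arm: 30 × 0.85 = 25.5.

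| Per arm | d = 0.75 | d = 0.86 |
|---|---|---|
| 25.5 (completers only) | 74.7% | 85.3% |
| 30 (all contribute fully) | 81.5% | 90.6% |

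The false-negative risk is one minus power: about 19% to 25% at 0.75 and about 9% to 15% at 0.86. With 25.5 per arm, 90% power needs d = 0.93.

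**5. Baseline adjustment.** Adjusting for a baseline value with correlation r to follow-up multiplies the residual SD by √(1 − r²). The effect detectable with 90% power is 0.866 at 29 per arm and 0.926 at 25.5.

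- 29 per arm: r = √(1 − (0.75/0.866)²) = 0.50.
- 25.5 per arm: r = √(1 − (0.75/0.926)²) = 0.59.

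**6. Attrition, a minor note.** 26/0.85 = 30.6, which rounds up to 31 per arm. Multiplying instead, 26 × 1.15 = 29.9, gives the 30 used. The gap is half a participant per arm (25.5 against 26).

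**The case against.** Four points can be made for the plan.

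- **The total was not built on 0.75.** It was built on 26 per arm, from the 0.86 effect, with a larger response expected for the combination. This stands. A reader might infer that the trial carries a 25% false-negative risk at its planning effect. The article does not support that: it has two planning effects, and the 25% belongs to 0.75 on completers only. At 0.86 the corresponding risk is about 15%.
- **Completers are not clearly the analysis set.** Section {20c} plans intention-to-treat with multiple imputation or a sensitivity analysis, sections {11b} and {18b} keep data collected before withdrawal, and section {20a} uses a mixed model over time. This stands too, so 25.5 per arm is a cautious bound. How much power would be recovered cannot be computed from the article. Full contribution from all 30 per arm still gives only 81.5% at 0.75.
- **The primary outcome is a change from baseline (Outcomes {12}), so adjustment may raise power.** It may, and it would be wrong to infer that no analysis could reach 90%. But the article gives no correlation, and its power sentence refers to a post-intervention difference. The 90% as stated does not rest on adjustment.
- **The effect-size unit is undefined.** SD units between arms is the natural reading, but it remains an assumption. The mismatch between the ratios 1.31 and 1.12 holds for any standardised between-arm effect under one test, level and power.

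The attrition shortfall is too small to count as a point of its own.

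**Conclusion.** The power statement is wrong as written. At 0.75 and 29 per arm the two-sided, unadjusted power is 80%, about ten percentage points below the figure given, and no unadjusted between-arm test of the kinds named reaches 90%. The 26 per arm at 0.86 corresponds to a different power, 86%.

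For the trial as enrolled, power lies between about 75% and 81.5% at 0.75, and between about 85% and 90.6% at 0.86. The lower ends count completers only and the upper ends assume that every randomised participant contributes fully. All these figures rest on SD units, a two-sided 5% test and no baseline adjustment.

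A reader might go further and conclude that the trial must be enlarged. That does not follow: the error lies in the stated power, and 30 per arm can be kept if the power is described correctly.

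**What to change.** Delete the 90% claim in Sample size {14} and replace it with wording such as:

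> Ninety randomised participants, with about 25 to 26 completers per arm after 15% attrition, give about 75% power (two-sided 5%, unadjusted, completers only) for a between-arm difference of 0.75 SD, 85% for 0.86 SD and 90% for 0.93 SD.

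If the baseline-adjusted or mixed-model analysis is meant to deliver 90% at 0.75, say so and give the baseline to follow-up correlation relied on: about 0.50 at 29 per arm, or about 0.59 at 25.5. State the effect-size unit and the sidedness in the same place.

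The cost is one rewritten paragraph and a less favourable stated power. No additional participants are needed, and the design, endpoint and analysis stay as they are.

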### Recruitment {15}

Participants will be recruited over 24 months. Potential participants will be identified by clinicians that are aware of the study, the principal investigator, or research staff who will review the clinical charts of patients attending the Pediatric Endocrinology Clinic, General Pediatric Clinic, and the Pediatric Centre for Weight and Health. Once a potential participant has been identified, a clinician or the principal investigator will approach the potential participant and their parents, provided information about the study, and ask the patient if his/her name can be passed onto a research team member to be contacted about the study. If the potential participant and their parents provide written consent to release contact information to researcher, the research team member will contact them to provide additional information about the study, answer questions or concerns, complete a screening process, and if applicable, arrange a potential study visit where written inform consent will be obtained. The informed consent process will be conducted in person by a qualified research team member.

In the case that a research staff member identifies a potential participant, the study coordinator will approach the attending physician and review this information. If the attending physician agrees, he/she will ask the patient if they might be interested in learning more about the research study. If the patient agrees, a member of the research team will be called to share the information and invite the patient to participate.

## Assignment of interventions: allocation

### Sequence generation {16a}

After having provided written informed consent/assent, participants will undergo a baseline assessment and be randomized to one of the three intervention groups A, B, and C (i.e. MET, FIBER, MET + FIBER) via computer-generated numbers and stratified by age and sex, using the adaptive (dynamic) randomization (Step 2, Fig. 3). Each group will be also randomly allocated to one of three intervention arms of MET, FIBER, and MET + FIBER (Step 3, Fig. 3). Staff who completed Steps 2 and 3 will be different and will be blinded to the other step. Stratification will be based on four sex/age categories of male 12–15 years old, female 12–15 years old, male 16–18 years old, and female 16–18 years old.

